## Abstract

**Background:**

Postoperative atrial fibrillation (POAF) is a frequent adverse event after thoracic surgery with associated morbidity, mortality, and healthcare costs. It has been shown to be preventable with prophylactic amiodarone, which is only recommended in high-risk individuals due to the potential associated side effects. Risk factors for POAF have been identified and incorporated into a prediction model to identify high-risk patients. Further evaluation in the form of a multicenter clinical trial is required to assess the effectiveness of prophylaxis specifically in this high-risk population. The feasibility of such a trial first needs to be assessed.

**Methods:**

The PREP-AF trial is a double-blind randomized controlled feasibility trial. Individuals undergoing major thoracic surgery who are identified to be high-risk by the POAF prediction model will be randomized 1:1 to receive a short course of amiodarone vs. placebo in the immediate postoperative period. The primary outcome is feasibility, which will be measured by the number of eligible patients identified, consented, and randomized; intervention adherence; and measurement of future outcomes of a full trial.

**Discussion:**

This study will determine the feasibility of a randomized controlled trial to assess the effectiveness of prophylactic amiodarone, in high-risk patients undergoing major thoracic surgery. This will inform the development of a multi-center trial to establish if prophylactic amiodarone is safe and effective at reducing the incidence of POAF. Preventing this adverse event will not only improve outcomes for patients but also reduce the associated health resource utilization and costs.

**Trial registration:**

ClinicalTrials.gov NCT04392921. Registered on 19 May 2020.

## Administrative information

The order of the items has been modified to group similar items (see http://www.equator-network.org/reporting-guidelines/spirit-2727-statement-defining-standard-protocol-items-for-clinical-trials/).

## Introduction

### Background and rationale {6a}

Postoperative atrial fibrillation (POAF) is the most commonly sustained arrhythmia after thoracic non-cardiac surgery [1, 2]. We found it occurred in 17% of patients after lobectomy, 23% after pneumonectomy, and 12% after esophagectomy, making it the most common postoperative adverse event after thoracic surgery at our institution [3]. It is associated with increased postoperative morbidity, length of stay, ICU admission, and mortality [1, 2]. For example, POAF is associated with increased mortality risk after esophagectomy (from 4.8 to 8.1%, *p* = 0.04) [4]. Recently, the results of two large multicenter randomized controlled trials (RCTs) (POISE-1: metoprolol vs. placebo and POISE-2: aspirin vs. placebo) were analyzed with regard to the impact of POAF. Among 18,117 patients (mean age 69 years, 57.4% male), 404 had POAF (2.2%). The stroke incidence 1 year after surgery was 5.58 vs. 1.54 per 100 patient-years in patients with and without POAF. Patients with POAF also had an increased risk of death (incidence 31.37 vs. 9.34; aHR 2.51, 95% CI 2.01–3.14; *P* < 0.001) and MI (incidence 26.20 vs. 8.23; aHR 5.10, 95% CI 3.91–6.64; *P* < 0.001) [5]. Given the frequent incidence after thoracic surgery and marked impact of POAF, prophylaxis to prevent POAF is of interest.

#### POAF prophylaxis and safety

Of the agents that have been used for prophylaxis, metoprolol and amiodarone are most effective at preventing POAF [2, 6]. Unfortunately, the use of metoprolol for prophylaxis in a generalized manner after non-cardiac surgery is associated with increased risk of stroke and death [7]. Amiodarone, a Class III anti-arrhythmic, has been extensively studied as a prophylactic agent for POAF, effectively reducing the rate of POAF by as much as 31% after thoracic surgery, with a total relative risk (RR) of 0.22 (*P* = 0.001; 95% CI, 0.09–0.54) and a NNT of 5.1 [6]. However, the safety of prophylactic amiodarone has also been controversial; high dosing regimens have been associated with hypotension, bradycardia, QT prolongation, and in patients undergoing pneumonectomy, adult respiratory distress syndrome (ARDS), in addition to more common effects of tremor, nausea, and constipation [8]. Several recent trials have suggested administration of low dose prophylactic amiodarone to patients undergoing non-cardiac thoracic surgery to be safe [9–13]. Given its effectiveness, but concern regarding toxicity, the Society of Thoracic Surgeons (STS) most recent 2011 guidelines only recommend amiodarone prophylaxis for patients undergoing esophagectomy, and pulmonary resection, excluding pneumonectomy, until additional data addressing its potential for pulmonary toxicity is available (class III recommendation) [14]. The American Association of Thoracic Surgeons 2014 guidelines recommends surgeons consider prophylactic amiodarone for the prevention of POAF for intermediate and high-risk patients undergoing pulmonary resection (class IIa recommendation) and for all patients undergoing esophagectomy (class IIb recommendation) to minimize potential side effects of amiodarone [1]. However, until recently, there have been no validated tools to identify patients at elevated risk of POAF.

#### Prediction of POAF

In reviewing the literature for risk stratification tools to predict POAF after thoracic surgery, we only identified one which was internally validated for all patients undergoing major thoracic surgery and contained factors obtainable in the preoperative period (resting heart rate, gender, and age) [4, 15, 16]. After evaluation of this tool at our institution in a sample of 2036 patients undergoing major thoracic surgery between 2008 and 2018, we found it to also be externally valid [17]. To facilitate identifying potential candidates for prophylaxis, we translated this POAF risk model into a designation of high vs low risk. Taking into account the cited importance of the extent of surgery in POAF incidence, we designated the “high risk” patients as individuals undergoing a procedure with extensive pericardial dissection (esophagectomy, pneumonectomy, and lobectomy) with a risk score of 4–6/6. This high risk group represented 51% all patients undergoing major thoracic surgery and experienced a fourfold higher incidence of POAF compared to the remaining “low risk” cohort (12.3% vs 3.4%, *p* < 0.001). If amiodarone provides a risk ratio of 0.22 (as demonstrated by the meta-analysis by Zhang et al.) in the “high-risk group”, it would reduce the POAF rate to 2.7% which would translate to a NNT of 10.4 [6].

While there is potential benefit of amiodarone in reducing POAF, there are risks with its administration and further research is needed to understand its effectiveness and safety in patients with increased risk of POAF as highlighted by the most recent guidelines [14]. An experimental randomized design is necessary to remove important biases and to augment the internal validity of the study to the point that it will be given adequate credence and effect on clinical practice. Our overall aim is to decrease the incidence of POAF after thoracic surgery by specifically targeting high-risk patients with best evidence prophylactic therapy.

### Objectives {7}

This study aims to assess the feasibility of a blinded, randomized controlled trial where patients at increased risk of POAF who are undergoing major thoracic surgery are randomized to receive prophylactic amiodarone or placebo. This is intended to inform the development of a multi-center randomized controlled trial to establish if prophylactic amiodarone is safe and effective at reducing the incidence of POAF after major thoracic surgery.

### Trial design {8}

The PREP-AF feasibility trial is a pragmatic single-center, parallel group, double-blinded, randomized controlled feasibility study.

Individuals will first be assessed for their risk of POAF based on their POAF prediction score (Table 1) and planned procedure.

**Table 1 Tab1:** POAF prediction score [15, 17]

Criteria	Points
Male gender	1
HR^a^ >72 bpm	1
Age 55–74 years	3
Age >75 years	4
Total	/6

^a^Heart rate (HR)

Individuals will be considered “high-risk” of POAF by meeting both of the following criteria: (1) POAF prediction score greater than or equal to 4 (Table 1) and (2) undergoing lobectomy, extended lobectomy, pneumonectomy, or esophagectomy.

High-risk individuals will be randomized 1:1 to intervention or control group.

Individuals will be considered “low-risk” of POAF by one the following criteria: (1) POAF prediction score less than 4 (Table 1) or (2) undergoing gastrectomy or sublobar resection.

Low-risk individuals will receive standard care with monitoring for clinical outcomes and adverse events.

Patients using beta-blockers at the time of enrollment will be eligible to participate in the trial. Given that beta-blocker use is protective against development of POAF, we will stratify these patients at the time of randomization to ensure the proportion of beta blocker usage is equal between intervention groups.

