#### Sample size {14}

No sample size calculation was conducted for this feasibility study. We aim to recruit 80 patients for randomization during this 12-month trial. Our institution conducts approximately 200 major thoracic surgeries annually and we anticipate 100 of those patients to be eligible for inclusion based on POAF risk and assume a recruitment rate of 80. Patients will follow the schedule activities described in the “Participant timeline {13}” section including a 30-day follow-up.

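### The age bands in Table 1 leave a gap at 75, so applying the printed score puts a patient aged 75 in completed years in the low-risk group, while patients aged 74 and 76 can qualify for randomisation

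*Protocol article*

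**What the plan says.** Trial design {8} defines risk by a score and a planned procedure. Table 1 gives 1 point for male gender, 1 point for a heart rate above 72 bpm, and age points in two rows: "Age 55–74 years 3" and "Age >75 years 4". The total is out of 6.

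High risk requires a "POAF prediction score greater than or equal to 4" together with lobectomy, extended lobectomy, pneumonectomy or esophagectomy. Low risk is defined by a "POAF prediction score less than 4 (Table 1) or (2) undergoing gastrectomy or sublobar resection". The same section then states: "High-risk individuals will be randomized 1:1 to intervention or control group". Low-risk patients receive standard care, and under Recruitment {15} they have no formal consent discussion.

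The background subsection on prediction of POAF names the three factors and gives the high-risk range as 4 to 6 out of 6, but not the age bands. It also says that the institution evaluated the score in 2036 of its own patients. Sample size {14} sets an aim of 80 randomised patients and says "we anticipate 100 of those patients to be eligible for inclusion based on POAF risk", out of about 200 operations a year.

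**The concern.** The lower age row stops at 74 and the upper row starts strictly above 75. In completed years, age 75 lies in neither and earns nothing. A score that otherwise rises with age falls to the level of a patient under 55 for one year and then jumps to its maximum age points.

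This matters because Table 1 is the threshold for entry to randomisation, not background text. If it is followed literally, patients at the edge of the score's highest age band go to standard care without being asked for consent. If screening staff repair the table themselves, the article does not tell them whether 75 earns 3 or 4 points, and two screeners could class the same patient differently. Outcomes {12} includes the proportions risk-stratified, screened and consenting among the feasibility measures, so the coding of the score feeds into what the study reports.

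**Working it through.** **Inputs** (all from Table 1 and the text below it in Trial design {8}): male = 1; heart rate above 72 = 1; age 55–74 = 3; age above 75 = 4; threshold for high risk = 4.

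**Step 1, reproduce the printed maximum.** 1 + 1 + 4 = 6, which agrees with the total given in Table 1.

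**Step 2, score by age in completed years.** Score = age points + sex (0 or 1) + heart rate (0 or 1), so each age has four sex and heart-rate combinations.

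| Age | Age points as printed | Possible scores | Combinations reaching 4 |
|---|---|---|---|
| 54 | 0 | 0, 1, 1, 2 | 0 of 4 |
| 74 | 3 | 3, 4, 4, 5 | 3 of 4 |
| 75 | 0 | 0, 1, 1, 2 | 0 of 4 |
| 76 | 4 | 4, 5, 5, 6 | 4 of 4 |

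At 75 the best possible score is 0 + 1 + 1 = 2, which is below 4 whatever the procedure.

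**Step 3, other readings of age.** If age is exact and decimal in both rows, 74.5 scores 0 to 2 and 75.5 scores 4 to 6. The gap then runs from just above 74.0 up to and including 75.0. If the lower row is in completed years and the upper row means any time after the 75th birthday, only the birthday itself is uncovered. A gap remains on each reading, but its width differs.

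**Step 4, what closing the gap does at age 75.**

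| Repair | Possible scores at 75 | Combinations reaching 4 |
|---|---|---|
| 75 joins the upper band (4 points) | 4, 5, 5, 6 | 4 of 4 |
| 75 joins the lower band (3 points) | 3, 4, 4, 5 | 3 of 4 |

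The repairs differ in classification for one combination only: a woman with a heart rate of 72 or below, who scores 4 under the first and 3 under the second.

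**Step 5, size.** The article gives no age distribution, so a share must be assumed. Take 2–5% of patients as aged 75.
- Of the roughly 100 eligible patients a year (Sample size {14}): 0.02 × 100 = 2 to 0.05 × 100 = 5.
- Of all patients having a qualifying procedure, using the mix in Study setting {9}: 200 × (0.52 + 0.05 + 0.11) = 136 a year; 0.02 × 136 = 2.7 to 0.05 × 136 = 6.8.
- Scaled to the aim of 80 randomised: 0.02 × 80 = 1.6 to 0.05 × 80 = 4.

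**Step 6, effect on the enrolment criterion.** Outcomes {12} asks for an average of at least one patient per week, about 52 a year. The aim of 80 is 80 / 52 = 1.54 per week; losing 4 leaves 76 / 52 = 1.46. The criterion is still met.

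**The case against.** The strongest reply is that this is a printing slip and not an operating fact. Table 1 reproduces a published score that the institution has already applied to its own patients. The full protocol and screening form are not shown and may carry the right bound. The article therefore establishes that the printed bands are not contiguous; it does not show that any patient has been or will be misclassified. That stands. It limits what can be said about consequences, but the published threshold still needs correction.

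A reader might go further and infer any of the following, none of which the article supports:

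- **Every 75-year-old is excluded.** This needs age in completed years in both rows and literal use of the table.
- **All of them are wrongly classed.** This presumes that 75 belongs to the upper band. If it belongs to the lower band, a woman with a heart rate of 72 or below is correctly low-risk.
- **The 80-patient aim is undermined.** The anticipated 100 eligible is close to the 51% high-risk share reported in the background (0.51 × 200 = 102). If that share was computed with the bands as printed, the 100 already reflects the gap and nothing further is lost.
- **The full trial will inherit the error.** Statistical methods {20a} plans to incorporate the results of this study into a full-scale trial. It does not say that the score table is carried over.

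It is also fair to say that classification happens before randomisation and without regard to arm, so the gap cannot bias the comparison of amiodarone with placebo.

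**Conclusion.** The point holds as an error in the stated entry rule: the bands do not meet, and no other part of the article corrects them. The finding for age 75 in Step 2 rests on completed years, the usual way of recording age at screening, and on use of the table as printed.

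The practical size is small and not computable from the article. The figure of a few patients a year depends entirely on the assumed 2–5% share, and it counts patients who fall in the gap, not patients shown to be misclassified. Any effect on the 80-patient aim depends on how the 51% was coded, and any effect on a full trial depends on the table being reused. The correction is worth making because the table governs who is randomised and its repair is not self-evident for every patient, not because a feasibility conclusion is at risk.

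**What to change.** Check the age bands against the score as coded in the institution's 2036-patient validation, and reprint Table 1 with contiguous bands. Changing the upper row to include 75 is the natural candidate, because the lower row already stops at 74, but the validation coding should decide. State that age is in completed years at a named time point, such as the screening visit. Use the same coding in the screening form and in the count of eligible patients behind the figure of 100, and confirm that the 51% high-risk share was derived with it.

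The cost is one character in Table 1, a matching entry on the screening form and a look-up in existing code. No extra patients, visits or procedures are needed.

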## Methods: participants, interventions, and outcomes

### Study setting {9}

This study will be conducted with the Division of Thoracic Surgery at The Ottawa Hospital, an academic teaching center in Ottawa, Ontario, Canada. At our center, approximately 200 patients undergo major thoracic surgery annually. Of which, 52% undergo a lobectomy, 25% a sublobar resection, 5% a pneumonectomy, and 11% an esophagectomy.

### Eligibility criteria {10}

All patients undergoing thoracic surgery will be screened for eligibility. In order to participate, patients must provide consent if “high-risk” of POAF, be ≥18 years, and undergoing major non-cardiac pulmonary or esophageal surgery at the Ottawa Hospital during the 1-year time period.

Patients will be excluded if they are <18 years; are pregnant; have a history of atrial arrhythmia, Wolf-Parkinson-White syndrome (WPW), or 2nd or 3rd degree heart bock without a pacemaker; are currently on antiarrhythmic therapy; have a previous severe adverse reactions or contraindications to amiodarone; have QTc interval longer than 450ms; or have serum alanine transaminase or aspartate transaminase over 3 times the upper limit of normal, or Child-Pugh class C liver dysfunction.

Patients enrolled in other clinical trials are potential candidates for PREP-AF feasibility.

### Who will take informed consent? {26a}

All eligible individuals will be approached for participation in the trial by a research coordinator during their preoperative visit to discuss the study protocol, review eligibility criteria, and assess willingness to participate. If high risk, a consent discussion will be initiated, including a discussion of the risk and benefits of participating in the trial.

### Additional consent provisions for collection and use of participant data and biological specimens {26b}

Not applicable.

### Interventions

#### Explanation for the choice of comparators {6b}

Placebo was selected as a comparator because no prophylactic agent is given as part of standard of care at our institution. In our survey of thoracic surgeons in Canada, only 5 of 67 respondents (7.4%) consider prophylaxis routinely.

#### Intervention description {11a}

Eligible high-risk patients will be randomized 1:1 to two treatment arms: *Intervention* patients will undergo the following: (a) postoperative day (POD) 0: receive 1050mg of amiodarone in 500mL of 5% dextrose in water (D5W) administered intravenously (IV) initiated at the time of anesthesia induction over 24 h at a rate of 0.73mg/min (43.75ml/h); (b) POD 1 to 5 or day of discharge (whichever occurs first):
*◦ If able to tolerate po intake:* 400mg po BID for postoperative days 1 to 5 or until the day of discharge (whichever occurs first).*◦ If unable to tolerate po intake:* 1050mg IV in 500mL of 5% dextrose administered over 24h for postoperative days 1 to 5 or until the day of discharge (whichever occurs first).

*Control* patients will receive identically marked IV infusions or oral capsules, containing D5W or placebo. These dosing regimens, in keeping with published protocols, are considered safe in thoracic surgery patients [9, 11].

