#### Concealment mechanism {16b}

Patients, physicians, nurses, and the research coordinator will be kept strictly blinded as to individual group allocation and treatment. The intervention, active or placebo, will be provided to the clinicians responsible for administration in concealed containers. The clinical trial Pharmacy Research Technician will be responsible for the coding and labeling of all containers and instructions for administering the intervention will be identical for both control and amiodarone groups.

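### The day-0 amiodarone infusion rate is printed as 43.75 ml/h, but the stated dose, bag and duration give 20.83 mL/h; the printed number is the mg/h rate with a volume unit

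*Protocol article*

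**What the plan says.** Intervention description {11a} gives five figures for the day-0 infusion. The first two are the dose and the bag: patients "receive 1050mg of amiodarone in 500mL of 5% dextrose in water (D5W"). The other three are the duration and the rates by mass and by volume: the drug is "administered intravenously (IV) initiated at the time of anesthesia induction over 24 h at a rate of 0.73mg/min (43.75ml/h").

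The same section repeats the bag for patients who cannot take oral drug on the following days: "1050mg IV in 500mL of 5% dextrose administered over 24h". It prints no rate for that option. No other section gives an infusion rate, another bag volume or a concentration.

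Concealment mechanism {16b} adds that "instructions for administering the intervention will be identical for both control and amiodarone groups". It contains no wrong figure, but it means that a rate written into those instructions would apply to both arms.

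**The concern.** The mass rate and the volume rate are meant to describe the same infusion, so the concentration of the bag must link them. It does not. The volume rate matches the hourly mass rate digit for digit, which points to ml written for mg.

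This is the only volume rate the article prints for the IV study drug, and it stands in the section that defines the intervention. The drug is an antiarrhythmic started at anesthesia induction. The article's own background links high-dose regimens to hypotension, bradycardia and QT prolongation, and {11b} makes each of these a reason to stop study drug. An infusion set to the printed volume rate would give the drug at about twice the stated speed and then leave about half the planned period without drug.

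Two further consequences are smaller. Intervention delivery is judged against a 90% adherence threshold (Outcomes {12}), and with two incompatible rates an infusion that follows one departs from the other. The study is also meant to lead to a multicenter trial and contribute its data to it (Statistical methods {20a}), so an uncorrected figure could be carried to other sites.

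**Working it through.** **Inputs**, all from Intervention description {11a}: dose 1050 mg; bag 500 mL; duration 24 h; printed mass rate 0.73 mg/min; printed volume rate 43.75 ml/h.

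**1. Reproduce the printed mass rate.** Dose / time = 1050 mg / (24 × 60 min) = 1050 / 1440 = 0.729 mg/min. This rounds to the printed 0.73, so dose, duration and mass rate agree.

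**2. Try to reproduce the printed volume rate.** Volume / time = 500 mL / 24 h = 20.83 mL/h. The printed 43.75 ml/h does not reproduce.

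**3. Cross-check through the concentration.** 1050 mg / 500 mL = 2.1 mg/mL. The printed mass rate then gives 0.73 × 60 / 2.1 = 20.86 mL/h, the same answer apart from the rounding of 0.73.

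**4. Find the source of 43.75.** Dose / time in hours = 1050 mg / 24 h = 43.75 mg/h exactly.

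**5. Look for a reading that would make 43.75 mL/h right.**
- Over 24 h it needs 43.75 × 24 = 1050 mL, a concentration of 1 mg/mL. The section states 500 mL for day 0 and again for the later IV option.
- If the drug's own volume is added on top of 500 mL (assumption: 50 mg/mL concentrate, so 1050 / 50 = 21 mL), the rate is 521 / 24 = 21.7 mL/h. That is still about half the printed figure.

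**6. Consequence if the printed volume rate were used, one 500 mL bag.**

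| Quantity | As intended | At 43.75 mL/h |
|---|---|---|
| Volume rate | 20.83 mL/h | 43.75 mL/h (ratio 43.75 / 20.83 = 2.10) |
| Mass rate per hour | 43.75 mg/h | 43.75 × 2.1 = 91.9 mg/h |
| Mass rate per minute | 0.73 mg/min | 91.9 / 60 = 1.53 mg/min |
| Time to empty | 24 h | 500 / 43.75 = 11.43 h |
| Planned period without infusion | 0 h | 24 − 11.43 = 12.57 h |
| Drug from one bag | 1050 mg | 500 × 2.1 = 1050 mg |

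**7. Who could be exposed.** With the target of 80 randomized 1:1 (Sample size {14}), 80 / 2 = 40 patients would be in the active arm. Placebo patients would receive dextrose faster but no drug.

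**The case against.** The arithmetic is not in dispute; the case on the other side concerns how much it matters.

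- **The slip can be recognized from its own sentence.** The four correct figures stand beside it, the later IV option repeats the same bag and duration, and 43.75 is plainly the mg/h value. This stands: a careful reader can tell which figure is wrong and what was intended. It does not make the figure safe to leave, because a volume rate may be copied on its own.
- **Harm depends on a step that is not shown.** This is a journal article, and bedside staff would work from pharmacy instructions that may carry the correct rate. This also stands. Nothing shows that any patient was or would be infused at 43.75 mL/h, and the figures in step 6 are conditional.
- **The effect is bounded.** One bag delivers 1050 mg at either rate. The protocol also has stopping criteria {11b}, continuous heart rate monitoring for 48 to 72 h {11d} and management plans for the expected adverse events {22}. These limit the consequences but do not correct the figure.
- **The recruitment target, randomization and analysis are untouched.** That is correct.
- **20.83 mL/h assumes a final volume of exactly 500 mL.** This is a fair point. With the assumed 21 mL of added drug volume the rate is 21.7 mL/h. The difference is small beside the error, and the pharmacy can settle it when it confirms the rate.

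**Conclusion.** The concern holds and should be fixed. The printed volume rate contradicts the other four day-0 figures. Taking 500 mL as the final bag volume, the correct rate is 20.83 mL/h and the printed one is 2.1 times too high. No volume or concentration elsewhere in the article rescues it.

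The error is in the administration rate, not in the dose per bag. Its clinical consequence would arise only if the volume figure were used to set an infusion, which the article neither shows nor excludes. It ranks above a clerical slip because it is the only volume rate given for an intravenous antiarrhythmic, in the section that defines the treatment.

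**What to change.** In Intervention description {11a}, replace the parenthetical volume rate with 20.83 ml/h (43.75 mg/h). State the same rate for the IV option on postoperative days 1 to 5, which uses the same bag and duration; dose, volume and time already imply it, but printing it removes doubt.

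Have the research pharmacy confirm that the order set and the administration instructions for active and placebo bags use 20.83 mL/h. If the drug volume is added on top of 500 mL, the pharmacy should supply the exact figure for the final volume.

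The cost is a one-line correction and one check of pharmacy documents. It needs no extra patients or procedures and no change to the analysis.
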